### Voluntary Withdrawal of Participants

(1) Participants who do not express the desire to withdraw from the study but cease to accept medication and testing are considered withdrawn.(2) Participants who cannot continue to participate in clinical research for personal reasons; perceive poor efficacy; exhibit intolerance due to adverse reactions; and for economic reasons.

Irrespective of the reason for withdrawal, the case record will be retained. The final test results will be used in the final analysis, and the curative effect and adverse reactions will be analyzed in the full dataset.

### Randomization and Data Collection

Patients who meet the criteria will be randomized into TWP and placebo groups. Randomized numbers will be generated by the central randomization system (http://www.tcmcec.net/crivrs/) established by the Clinical Evaluation Center of the Chinese Academy of Traditional Chinese Medicine. The randomized numbers will be ordered based on a given sequence, and patients will be divided into two groups according to the randomized numbers. The probability of participants being assigned to each group or center is not fixed but will be adjusted according to certain conditions. The electronic case report form (eCRF) was established by the Clinical Evaluation Center of the Chinese Academy of Traditional Chinese Medicine. All data will be recorded by the investigator in a CRF and eCRF. Furthermore, a unique random allocation is assigned using a system involving double blinding for participants and researchers. Every follow-up will be required to be logged into the central stochastic system by the investigator and into the central random system to obtain a drug number. The same platform will be used to collect information on the participants, random distribution, and assigned drugs to ensure random and blind methods are implemented and the test results are objective, to improve the quality of the clinical trial.

### Blinding Method

The central randomization system uses a randomly permuted block design, which includes subject screening, randomization, emergency exposure of blindness, designated drug, and drug supply. Blinding of the investigators, participants, statistician, staff in charge of data collection and clinical research associates will be blinded to the group assignments to avoid bias. In order to perform blinding, the placebo is processed into the same appearance, size, color, dosage form, weight, taste, and even smell like the same as the drug (TangWang prescription) in the treatment group. During the study, if participants experience severe adverse events, investigators will carry out an unblinding and perform urgent management accordingly. Statistician and staff in charge of data collection and clinical research associates, will all be third-party staff who did not involve in the design or patient recruitment of this study.

### Intervention Method

After grouping, participants will receive basic treatment including diabetes education, exercise and diet, as well as rational control of blood glucose, lipids, according to the 2017 diagnosis and treatment guidelines for the type 2 diabetes in China (Jia et al., 2019) and the 2020 American Diabetes Association guidelines (American Diabetes Association, 2020). In this work, according to the Chinese guidelines for exercise treatment of diabetes mellitus (Sun and Liu, 2013), If there are the following situations in patients: diabetic ketoacidosis, fasting blood glucose greater than 16.7 mmol/l, proliferative diabetic retinopathy, diabetic nephropathy and severe arrhythmia and transient ischemic attack, these patients could not be recommended to receive the exercise treatment. Furthermore, participants can choose the appropriate exercise style according to their preferences. All patients’ exercise patterns and exercise time will be recorded in detail. All the participants will be administered oral calcium dobesilate capsules (Ebewe Pharma Ges.m.b.H.Nfg KG, 0.5 g three times per day). The study group will be received TangWang prescription (one bag twice a day) and the control group will be treatment with placebo (one bag twice a day). The treatment duration is set at 48 weeks, and the study medications will be labeled by pharmacists according to the randomized list generated by the central randomization system. The management of TWP and the placebo will be assigned to a special pharmacologist in the hospital. The schedule of enrollment, interventions, and assessments is shown in Table 1.

**TABLE 1 T1:** The schedule of enrollment, interventions, and assessments.

	Study period														
	Enrollment	Allocation	Post-allocation(w)												Close-out
Timepoint	-7-0		4	8	12	16	20	24	28	32	36	40	44	48	**t** _**x**_
Enrollment															
Eligibility screen	X														
Informed consent	X														
Allocation		X	X												
Interventions															
TangWang prescription															
Placebo															
Assessments															
Baseline	X	X	X												
Vital sign physical examination															
Routine ophthalmic examination fundus examination	X	X	X						X						X
Color fundus photography	X	X	X						X						X
Fluorescence fundus angiography	X	X	X						X						X
Optical coherence tomography	X	X	X						X						X
Vision															
Fasting blood-glucose, blood pressure															
Routine blood test and routine urine test stool routine examination	X	X	X						X						X
ECG, liver and kidney function, glycosylated hemoglobin, blood lipid	X	X	X			X			X			X			X

### Data Monitoring and Quality Control

The designated clinical research coordinator (CRC) will inspect and monitor the SOPs used in the research study. For the clinical research, a CRC will be appointed to regularly conduct on-site inspection visits to the hospitals to ensure strict adherence to all conditions of the research program and check the original data to ensure consistency with the CRF. This study will be supervised by a full-time Contract Research Organization (CRO) company. The study set up will include a data audit committee to audit the research data and research SOPs. Each audit will include at least one Project Manager and one project elite.

### Outcome Evaluation

#### Primary Outcome

The primary outcome of the study is the changes in the degree of retinal microaneurysm lesions before and after treatment. This will be determined according to the following scale: none, mild non-proliferative phase, moderate non-proliferative phase, severe non-proliferative phase, and proliferative phase, which are divided into aggravated, unchanged, and reduced conditions. The aggravated state is defined as retinal microaneurysm lesions with a degree of severity > grade 1 after treatment. The unchanged state was defined as a degree of retinal microaneurysm lesions before and after treatment that is unchanged, while the reduced state is defined as a degree of retinal microaneurysm lesions that is reduced by >1 grade after treatment.

### Secondary Outcome

Change in the number of microhemangioma in DR.Change in the area of microaneurysm bleeding in DR.Change in the area of microaneurysm leakage in DR.Degree of change of macular edema in DR.Change in vision before and after treatment.

Color fundus photography, fundus fluorescein angiography, and coherent optical tomography will be performed every 6x months. Furthermore, the Early Treatment Diabetic Retinopathy Study (ETDRS) international visual acuity test will be performed every month.

### Safety Evaluation

The blood pressure, fasting blood glucose, vital signs, physical examinations, vision tests, electrocardiogram, liver function (alanine aminotransferase, aspartate aminotransferase, gamma-glutamyl transferase, alkaline phosphatase, and total bilirubin) and renal function (blood urea nitrogen and urine creatinine) will be monitored monthly. Glycated hemoglobin and blood lipids will be determined every 3 months) while routine eye and fundus examinations, including intraocular pressure, anterior segment, lens, and vitreous body, optical coherence tomography every 6 months, vitreous body need to be monitored to describe the conditions of opacity. The schedule of enrollment, interventions, and assessments is shown in Table 2.

**TABLE 2 T2:** The flow of the clinical data collection.

Visit	Project	Screening period/baseline	Visits 1–2,4–5,7–8,10–11	Visits 3,9	Visit 6	Visit 12
Visit time	-7-0 days	Medication 4, 8, 16, 20, 28, 32, 40, 44weeks ± 7 days	Medication 12, 36 weeks ± 7 days	Medication 24 weeks ± 7 days	Medication 48 weeks ± 7 days
Collect basic medical history					
Sign informed consent	×				
Fill in general information	×				
History of disease treatment	×				
Included inclusion and exclusion criteria	×				
vital Sign	×	×	×	×	×
physical Examination	×	×	×	×	×
merge Disease and medication	×	×	×	×	×
Diagnosis and monitoring					
Urine pregnancy test	×				
fasting Blood-glucose, blood pressure	×	×	×	×	×
glycosylated hemoglobin, blood lipids	×		×	×	×
Routine ophthalmic examination, fundus examination	×			×	×
Observation of effectiveness					
Color fundus photography	×			×	×
Fluorescence fundus angiography	×			×	×
Optical coherence tomography	×			×	×
Vision	×	×	×	×	×
Physico-chemical examination					
Routine blood test and routine urine test	×			×	×
Stool routine examination	×			×	×
Vital sign	×	×	×	×	×
Electrocardiogram, liver and kidney function	×		×	×	×
Adverse event		×	×	×	×
Other work					
Random grouping	×				
Distribute drug and patient’ diary card	×	×	×	×	
Recover drug, quantity statistics		×	×	×	×
Retrieve Patient’ diary card		×	×	×	×
Conclusion of research					×

Any adverse event (AE) will be dealt with carefully, analyzed, and measures will be taken to protect all participants. AEs will be recorded in the CRF according to the situation, and the record includes observations such as its duration, recurrence, and disappearance. If serious AEs (SAEs) occurs, the investigator must report them to higher authorities immediately and fill out the “Severe Adverse Event (SAE)” form. This study defines pregnancy as an SAE, indicating that:(1)During the study, any pregnancy event will be recorded in the corresponding data form by the researcher according to the SAE reporting procedure within the shortest time when the pregnancy event is discovered, and follow-up the outcome.(2)During the study, any abortion, whether accidental, natural or drug-induced will be reported as an SAE.(3)Any congenital abnormalities or congenital disabilities of neonates of a study participant will also be reported as an SAE. When participants experience emergencies, the main investigator can break the blind condition according to the drug and symptoms, institute relevant measures, and record the information in the CRF carefully.

### Sample Size Calculation

According to preliminary research data (Lian et al., 2015), the rate of retinal microvascular disease was reduced by 3.6% in the placebo group, and we predicted that the rate of retinal microvascular disease would be reduced by 8.9% in the TangWang prescription group. Therefore, the sample content formula was estimated using two overall rate hypothesis tests: Assuming that α = 0.05 and β = 0.10 according to the one-sided test, to obtain the tabular value, uα = 1.64485 and uβ = 0.84162, the data will be placed in the formula to obtain an n = 166.82. Therefore, each group needs 167 participants and considering a drop-out rate of no more than 15%, and each group would need 192 participants, for a total of 384 participants.

Furthermore, the rate of retinal microaneurysms disease increased by 3.6% in the placebo group, and according to the above formula, we would need n = 108.78 patients. Therefore, each group requires 109 participants, and if we assume a drop-out rate of no more than 20%, each group needs 132 participants for a total of 264 participants. Based on these two conclusions, 384 participants will be included in this study.

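### The sample-size section declares β = 0.10 but computes with the normal quantile for β = 0.20, so the stated type II error was not built into the comparison that fixes 384 participants

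*Protocol article*

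**What the plan says.** The Sample Size Calculation section of the protocol article sizes the trial on two rates. It takes from preliminary data that "the rate of retinal microvascular disease was reduced by 3.6% in the placebo group" and predicts that "the rate of retinal microvascular disease would be reduced by 8.9% in the TangWang prescription group". The error rates and their quantiles stand in one sentence, which sets α = 0.05 and continues "β = 0.10 according to the one-sided test, to obtain the tabular value, uα = 1.64485 and uβ = 0.84162". The same sentence ends with the result, n = 166.82. This is rounded up to 167 per group, and then "considering a drop-out rate of no more than 15%, and each group would need 192 participants, for a total of 384 participants".

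A second calculation concerns an increase of 3.6% in the placebo group: "according to the above formula, we would need n = 108.78 patients". Its second rate is not printed. It leads to 264 in total, and the larger total, 384, is adopted.

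The Statistical Analysis section makes all tests two-sided with p < 0.05 and compares the groups on the main outcome by a chi-square test. No other place in the article states a power or a different β.

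**The concern.** β and uβ are the same quantity in two forms, and the two printed forms disagree. The uα in the same sentence, 1.64485, is correct for one-sided 0.05, so no unusual table convention explains the mismatch.

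β is the declared risk of missing the planned effect. A reader, an ethics committee or a funder would take from β = 0.10 that a true difference of 3.6% against 8.9% would be missed one time in ten. If the arithmetic allowed more than that, a null result could be given more weight as evidence of no effect than the design supports.

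**Working it through.** **Inputs (Sample Size Calculation):** rates 3.6% and 8.9%; uα = 1.64485; uβ = 0.84162; stated β = 0.10; printed n = 166.82 and 108.78. From Statistical Analysis: two-sided 0.05, so the critical value is 1.95996.

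**1. Which β belongs to 0.84162?** 1 − Φ(0.84162) = 0.2000 and 1 − Φ(1.28155) = 0.1000. The printed quantile is the one for β = 0.20.

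**2. Reproduce the printed sizes.** The article does not print its formula. The following one reproduces both results:

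n = [uα·√(p̄q̄) + uβ·√(p1q1 + p2q2)]² / (p1 − p2)²

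- First comparison, 3.6% and 8.9%: p̄ = 0.0625, √(p̄q̄) = 0.24206, √(p1q1 + p2q2) = √(0.034704 + 0.081079) = 0.34027. The numerator is (1.64485 × 0.24206 + 0.84162 × 0.34027)² = (0.39815 + 0.28638)² = 0.46858. Divided by 0.053² = 0.002809, this gives **166.82**.
- Second comparison, 3.6% and 0% (the 0% is inferred): p̄ = 0.018, √(p̄q̄) = 0.13295, √(p1q1 + p2q2) = 0.18629. The numerator is (0.21868 + 0.15679)² = 0.14098. Divided by 0.036² = 0.001296, this gives **108.78**.

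Two matches to two decimals show that 0.84162 entered the arithmetic and is not a misprint beside an n computed with 1.28155.

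**3. Change only uβ, to 1.28155.**

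- First comparison: (0.39815 + 0.43607)² / 0.002809 = **247.8** per group, against 166.82 (+49%).
- Second comparison: (0.21868 + 0.23874)² / 0.001296 = **161.4** per group, against 108.78 (+48%). The adopted 167 per group exceeds this; by the same formula 167 gives about 91% power here.

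**4. What does 384 give for 3.6% against 8.9%?** The standard two-proportion formula has √(2p̄q̄) in the first term where the reproducing formula has √(p̄q̄). With the factor 2, √(2p̄q̄) = 0.34233, and at one-sided 0.05 with uβ = 0.84162, n = (0.56308 + 0.28638)² / 0.002809 = 256.9, about **257 per group** for 80% power.

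Power follows from z = [0.053·√n − u·0.34233] / 0.34027, where u is 1.64485 (one-sided) or 1.95996 (two-sided):

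| Evaluable per group | One-sided 0.05 | Two-sided 0.05 (planned test) |
|---|---|---|
| 167 | z = 0.358, 64% | z = 0.041, 52% |
| 192 (no loss) | z = 0.503, 69% | z = 0.186, 57% |

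**The case against.** The strongest defence is that this is a one-digit slip in a label. Both printed sizes follow from the printed uβ, no analysis rule depends on β, and the article never prints the words 90% power; that figure is inferred from β. On this view the authors meant 0.20, and one character settles it. It stands that the conflict may have begun as a labelling error. It does not stand that relabelling settles it.

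A reader might infer that the trial really has 80% power, or about 84% at 192 per group. Those values come only from the formula without the factor 2. By a standard formula 167 per group gives 64% one-sided, so writing β = 0.20 (80% power) would replace one wrong figure with another.

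A reader might also infer that the declared 10% was missed for every comparison. The article's figures do not support that. By the formula behind them, the second comparison needs 161.4 per group at β = 0.10, and 167 covers it. A standard formula gives about 80% one-sided there at 167, but that loss comes from the missing factor, not from uβ.

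Finally, a reader might attribute to this error the roughly 355 per group that a standard formula requires for β = 0.10 one-sided. That number combines two defects. The quantile alone accounts for the move from 166.82 to 247.8.

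**Conclusion.** The contradiction is real and sits within one sentence. The declared type II error of 0.10 was not used; the quantile for 0.20 was. For the comparison that sets the trial size, the wrong quantile alone understates the requirement by about 81 per group (247.8 − 166.82) in the protocol's own formula. For 3.6% against 8.9%, 384 participants give about 52% to 57% power under the planned two-sided test, or 64% to 69% one-sided, for 167 to 192 evaluable per group.

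This rests on three assumptions: the reproducing formula is the one used, which two exact matches support; the unprinted second rate is 0%, which affects only the second comparison; and the primary outcome is compared as two proportions, as the sample-size section does.

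**What to change.** In Sample Size Calculation, keep 384, remove the β = 0.10 claim, and state the power that 384 gives for 3.6% against 8.9% by a standard two-proportion formula under the two-sided 0.05 test of Statistical Analysis: about 52% with 167 evaluable per group and 57% with 192. The one-sided figures, 64% and 69%, can be given beside them. Do not simply relabel to β = 0.20 (80% power).

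The cost is a short edit and a less favourable stated power; no extra patients or procedures are needed. Keeping β = 0.10 instead would not be free. Even in the protocol's own formula it means 248 per group, and with the article's inflation 248 × 1.15 = 285.2, about 570 in total against 384. That formula would still lack the factor 2.

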## Abstract

**Background:** Diabetic retinopathy (DR) is one of the most common and severe microvascular complications of diabetes mellitus (DM), which results in blindness among adults worldwide. Presently, the efficacy of drug treatments for diabetic retinopathy (DR) is not satisfactory, thus urgently necessitating effective drug treatment measures. TangWang prescription (TWP) has been found to have retinal protection effects in previous clinical and basic research. However, there is a lack of rigorous, randomized, and controlled studies. This study aims to evaluate the efficacy and safety of TWP in delaying the development of DR.

**Methods:** This study is a randomized, double-blind, placebo-controlled, parallel-group, multicenter clinical trial, consisting of 384 participants to be randomized in a 1:1 ratio in the treatment and control groups. Furthermore, the treatment and control groups will be administered the TangWang prescription and the placebo, respectively, each at a dose of one bag twice a day. The study period will last for 48 weeks. The primary outcome measure will be the changes in the degree of retinal microvascular lesions before and after treatment. The secondary outcome will be changes in the degree of hemangioma, microvascular bleeding, microvascular leakage, macular edema, and vision. All statistical tests will be two-sided, and a *p* < 0.05 will be considered statistically significant.

**Discussion:** We hypothesize that the patients with DR will benefit from TangWang prescription, and in addition to the central random system and platform of dynamic information collection, the patients’ conditions will be monitored, and the data collected for analysis. If successful, this study will provide evidence that the TWP formulation delays in the progression of DR.

**Trial registration:** The design of this trial has been registered with the ClinicalTrials.gov (NCT03025399).

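### The printed n = 166.82 per group does not follow from 3.6% versus 8.9%; the printed quantiles give about 255 to 258, and 384 patients give about 51–58% two-sided power for that contrast

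*Protocol article*

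**What the plan says.** The calculation is in the Sample Size Calculation section of the protocol article.

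- **Rates.** For placebo, "the rate of retinal microvascular disease was reduced by 3.6% in the placebo group". For the active arm, the prediction is that "the rate of retinal microvascular disease would be reduced by 8.9% in the TangWang prescription group".
- **Method.** "the sample content formula was estimated using two overall rate hypothesis tests", that is, a comparison of two proportions.
- **Error rates.** "α = 0.05 and β = 0.10 according to the one-sided test", followed by the tabulated quantiles "uα = 1.64485 and uβ = 0.84162".
- **Result.** "the data will be placed in the formula to obtain an n = 166.82", rounded up to 167 per group.
- **Drop-out.** "considering a drop-out rate of no more than 15%, and each group would need 192 participants", making 384 in total.
- **Allocation (Abstract).** "384 participants to be randomized in a 1:1 ratio in the treatment and control groups".

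A second calculation, for worsening, gives 109 per group and 264 in total. The larger of the two totals, 384, is adopted. The Statistical Analysis section makes all tests two-sided at 0.05 and compares the main outcome between groups with a chi-square test.

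**The concern.** The section prints everything that a two-proportion sample size needs: both rates, both quantiles and the allocation. The answer can be checked directly, and 167 per group looks far too small for a difference of 5.3 percentage points between rates this low.

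The 384 rests on this figure alone, because the second calculation asks for only 264. If 166.82 is wrong, the trial does not have the power it claims for the effect it predicts. Readers who trust the stated β would then take a non-significant result as evidence against TWP when it could easily be a miss.

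**Working it through.** **Inputs** (Sample Size Calculation; allocation from the Abstract): p₁ = 0.036, p₂ = 0.089, difference 0.053, mean rate 0.0625, uα = 1.64485, uβ = 0.84162, 1:1. The two percentages are read as the proportions of patients with a reduced grade in each arm. They are the only pair of rates given.

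**Step 1: try to reproduce 166.82.**

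- p₁(1−p₁) + p₂(1−p₂) = 0.034704 + 0.081079 = 0.115783
- (uα + uβ)² = 2.48647² = 6.18253
- difference² = 0.002809

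| Formula, printed quantiles | n per group |
|---|---|
| Unpooled: 6.18253 × 0.115783 / 0.002809 | 254.8 |
| Mixed (pooled variance with uα, unpooled with uβ) | 256.9 |
| Pooled: 6.18253 × 2 × 0.0625 × 0.9375 / 0.002809 | 257.9 |
| Arcsine | 246.2 |
| Mixed with continuity correction | 293.4 |

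None gives 166.82. The first four differ among themselves by about 12 patients, whereas the gap to the printed figure is about 80 to 90.

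**Step 2: try other readings of α and β.** The printed uβ = 0.84162 is the quantile for β = 0.20, while the text states β = 0.10, whose quantile is 1.28155. The calculation is also one-sided and the analysis two-sided. Every alternative moves n further from 166.82 (range: arcsine to pooled):

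| Reading | n per group |
|---|---|
| One-sided 0.05, β = 0.10 | 341–357 |
| Two-sided 0.05, β = 0.20 | 313–327 |
| Two-sided 0.05, β = 0.10 | 418–438 |

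**Step 3: solve backwards.** With the printed quantiles and 3.6% on placebo, n = 166.82 requires a TWP rate of 10.3% (arcsine) to 10.6% (pooled). No such rate appears in the document.

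**Step 4: drop-out.** 167 × 1.15 = 192.05, which is the printed 192. To keep 167 after a 15% loss needs 167/0.85 = 196.5, so 197. Conversely, 192 × 0.85 = 163.2, so about 163 remain, below the plan's own 167.

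**Step 5: power at 384 for 3.6% versus 8.9%.** Normal approximation: power = Φ{[0.053√n − z√(2 × 0.0625 × 0.9375)] / √0.115783}, where the two square roots are 0.34233 and 0.34027.

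- n = 192, two-sided: (0.7344 − 1.95996 × 0.34233)/0.34027 = 0.187, power 57%
- n = 163, two-sided: (0.6767 − 1.95996 × 0.34233)/0.34027 = 0.017, power 51%

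| Per group | One-sided (exact) | Two-sided (exact) |
|---|---|---|
| 192, all analysed | 69% (71%) | 57% (58%) |
| 163, after 15% loss | 63% (65%) | 51% (51%) |

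The exact values enumerate the binomial outcomes of the Pearson chi-square test. The table separates two losses. With all patients analysed, the wrong n alone brings one-sided power to 69%, and testing two-sided takes it to 57%.

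**Step 6: detectable rate.** At 80% power, two-sided, with 3.6% on placebo, the same formula gives a TWP rate of about 11.0% with 192 per group and 11.9% with 163.

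**The case against.** No reading of the document restores 166.82. The serious objections concern how far the power figures reach.

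- **The primary outcome has three categories.** The Primary Outcome section classifies patients as aggravated, unchanged or reduced, so the chi-square test may have two degrees of freedom. Its power then also depends on worsening rates that the document does not give. As assumed illustrations, with 10% worsening in both arms the power is about 41% (163 per group) to 47% (192). With 20% on placebo against 10% on TWP it is about 79% to 85%. This stands: 51–58% is the power for the reduced-versus-not contrast on which the protocol sizes the trial, not for every version of the primary test. It does not rescue the printed n, which is a two-rate calculation.
- **The full analysis set keeps drop-outs.** It includes everyone randomised and treated at least once, and carries observations forward. About 192 per group may then count, which makes 57–58% the relevant figure; 51% fits an analysis of completers. This also stands, so both figures should be shown. Neither is near 80% or 90%.
- **A rate may simply be mistyped.** A TWP rate of 10.3–10.6% would explain 166.82. This is possible, but the section would still need correcting.
- **The drop-out slip is small.** It is five patients per group, about one percentage point of power (57.4% at 192, 58.5% at 197). Agreed; it is secondary.
- **An article condenses the full protocol.** That excuses omissions. Here the inputs and the answer are both printed and disagree.

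**Conclusion.** The concern holds. From the printed rates and quantiles, n is about 255 to 258 per group (246 by arcsine, 293 with continuity correction), not 166.82, and no reading of α and β in the document closes the gap. With 384 patients, the two-sided 0.05 chi-square test of 3.6% against 8.9% has about 57–58% power with full retention and about 51% after the plan's own 15% loss. Neither the stated 90% nor the 80% implied by the printed uβ is reached, even one-sided. If TWP works exactly as predicted, the chance of missing it is about 42–49%.

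This rests on reading 3.6% and 8.9% as the proportions improving in each arm, and on comparing improved with not improved. The source of 166.82 cannot be identified from the document.

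**What to change.** 1. If other rates or another formula produced 166.82, print them, so that the figure can be reproduced.
2. Otherwise withdraw 166.82, keep 384, and restate the power. Suggested text: *With 192 patients randomised per group and a two-sided α of 0.05, power to detect 8.9% against 3.6% is about 57% if all are analysed and about 51% if 15% are lost (163 per group). Power of 80% applies to a TWP rate of about 11.0% (192 per group) or 11.9% (163 per group) against 3.6%.*
3. Name the outcome contrast and the analysis set to which the power refers, make β agree with uβ, and use the same sidedness as the analysis.
4. Inflate for drop-out by n/(1 − d), not n(1 + d).

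The detectable rates describe what 384 patients can show; they are not a justification of that effect as a target. If the sponsor prefers to keep 8.9% with 80% two-sided power, the requirement is about 327 per group before drop-out, or 327/0.85 = 385 per group after it.

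The cost of items 1 to 4 is protocol wording and a less favourable power statement. They need no added patients and no change to treatment or analysis.

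### The drop-out allowance is applied as n × (1 + rate), with two unexplained ceilings (15% and 20%): at 15% loss, 192 per group leaves 163 completers, not the stated 167

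*Protocol article*

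**What the plan says.** The protocol article, under Sample Size Calculation, gives two calculations for the one trial.

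- **First paragraph.** From n = 166.82 it concludes that "each group needs 167 participants and considering a drop-out rate of no more than 15%, and each group would need 192 participants", 384 in total.
- **Second paragraph.** From n = 108.78 it concludes that "each group requires 109 participants", and that "if we assume a drop-out rate of no more than 20%, each group needs 132 participants for a total of 264 participants".

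It then combines them: "Based on these two conclusions, 384 participants will be included in this study". The Abstract gives the same total with 1:1 allocation: "384 participants to be randomized in a 1:1 ratio in the treatment and control groups". No reason is given for the different loss rates.

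**The concern.** Two things look wrong, and neither depends on how 167 and 109 were obtained.

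First, the two paragraphs describe the same randomised participants over the same 48 weeks of treatment, yet they allow for different maximum losses.

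Second, a drop-out allowance should ensure that the required number remains after the stated loss. Raising n by the loss percentage does not do this, because the loss is then taken from the larger, inflated number. The stated requirement is therefore not met at the stated ceiling in either paragraph.

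What is at stake is the accuracy of the number of participants with an observed end-of-study grade. The allowance is not idle here. The Drop-Out Criteria are broad: they include progression to proliferative disease, laser treatment, loss of vision, compliance outside the permitted range and use of prohibited drugs. The Discussion itself names poor compliance over the long treatment period as a limitation.

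**Working it through.** **Inputs, all from Sample Size Calculation**

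| | First calculation | Second calculation |
|---|---|---|
| Required per group | 167 (from 166.82) | 109 (from 108.78) |
| Loss ceiling | 15% | 20% |
| Stated per group | 192 | 132 |
| Stated total | 384 | 264 |

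**Step 1. Reproduce the plan's figures with n × (1 + rate).**
- First: 167 × 1.15 = 192.05, or 166.82 × 1.15 = 191.84. Either gives the stated 192.
- Second: 109 × 1.20 = 130.8, so 131. The stated 132 is one more, so even this method does not give it exactly.

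**Step 2. Apply n/(1 − rate).**
- First: 167 / 0.85 = 196.5, so 197 per group (394 in total).
- Second: 109 / 0.80 = 136.25, so 137 per group (274 in total).

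**Step 3. See what the stated numbers leave.**
- First: 192 × 0.85 = 163.2, so 163 completers, 4 short of 167.
- Second: 132 × 0.80 = 105.6, below 109.

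**Step 4. Find the loss that the stated numbers can bear.**
- First: 1 − 167/192 = 13.0%, against a ceiling of 15%.
- Second: 1 − 109/132 = 17.4%, against a ceiling of 20%.

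**Step 5. Size.**
- First: 197 − 192 = 5 randomised per group, and 5/192 = 2.6%.
- Second: 137 − 132 = 5 per group. Since 274 is still below 384, the first calculation governs whichever figure is used.

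**Step 6. Conditional case.** If 20% were the ceiling for the whole trial, 192 × 0.80 = 153.6, so 153 completers. The protocol does not say that this rate applies to the calculation needing 167.

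**Step 7. Why no power figure is attached.** With rates of 3.6% and 8.9%, the mean rate is 0.0625 and the difference 0.053. The plan's 166.82 is reproduced by

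(1.64485 × √(0.0625 × 0.9375) + 0.84162 × √(0.036 × 0.964 + 0.089 × 0.911))² / 0.053² = 166.8.

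The usual two-proportion formula has 2 × 0.0625 × 0.9375 under the first root. With that factor restored, the same inputs give about 257 per group. Power read off the plan's formula at 163 or 167 would therefore be too high.

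**The case against.** The best defence is that the error hardly matters. At the 15% attached to the first calculation the gap is 4 completers per group. Both rates are ceilings, and any loss up to 13.0% still leaves 167. Adding the percentage to n is a common shortcut. All of this stands, and it sets the size of the point. It does not make the statement correct, because the allowance fails at the ceiling for which it was set.

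A second defence is that drop-outs are not lost to the analysis. Under Statistical Analysis, the full analysis set holds everyone randomised and treated at least once, with the closest observation carried forward. This also stands, so 163 is a worst-case count of completers and not the denominator of that analysis. But carry-forward does not create an observed outcome. Table 2 schedules fundus photography and angiography only at baseline, week 24 and week 48, so a participant lost before week 24 has only the baseline grade to carry. Efficacy is also analysed in the per-protocol set.

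Two stronger readings are tempting, and the document supports neither:

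- **That the trial will have only 153 per group against 167.** This applies the 20% ceiling to a calculation to which the protocol does not tie it. The protocol ties 20% to the requirement of 109, which 153 exceeds by 44.
- **That the shortfall costs a little power from a level near 80%.** Such figures come from the formula without the factor 2 in the pooled variance (step 7), so they would lend support to a power that the plan's inputs do not give.

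**Conclusion.** The passage is wrong as written, but the error is small. The allowance is applied as n × (1 + rate), exactly in the first calculation and approximately in the second. The same participants are also given two loss ceilings without explanation.

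At 15%, 192 per group leaves 163 completers, 4 short of the stated 167, and 197 would be needed to keep 167. In the second calculation 132 leaves 105.6 against 109, with no effect on the total of 384.

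The result takes 167 and 109 as given and assumes that loss reaches its stated ceiling. It says nothing on whether 167 is adequate. That is a separate and larger problem in the same section.

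**What to change.** 1. State one drop-out ceiling for the trial and use it in both paragraphs. If the two rates are meant to differ, say why.
2. Apply n/(1 − rate) in both. At the rates now stated this gives 197 in place of 192 and 137 in place of 132 (274 in place of 264).
3. If 384 is kept, say what it delivers: 163 completers per group at 15% loss, or 167 if loss is at most 13.0%. If 20% is chosen as the single rate, the completer count to state is 153.
4. Correct the derivation of 167 separately, and apply the same n/(1 − rate) step to whatever n results. Until then, attach no power figure to 163 or 167.

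Items 1 to 3 cost a few restated figures in one section and a slightly less favourable completer count. They require no extra enrolment and no change to the analysis. Item 4 is a separate correction and may change n itself.
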